## Abstract

**Background:**

Antibiotic resistance is a global health challenge and the close correlation between antibiotic use and the development of resistance makes it essential to maintain a rational use of antibiotics. Most antibiotics are prescribed in general practice against acute respiratory tract infections (ARTI), even though most of these infections are of viral etiology. Thus, a safe method to substantially reduce unnecessary use of antibiotics in general practice is needed. Procalcitonin (PCT) is a precursor protein with very low circulating levels in the blood under physiological conditions. However, in response serious bacterial infection the level of PCT in the blood may increase significantly. Until recently, quantitative analyses of PCT was performed in hospital laboratories, impeding the implementation of PCT in primary care. Our aim is to determine whether it is possible to lower the use of antibiotics in patients presenting with symptoms of ARTI, without significantly prolonging the period of illness, by using a newly released PCT point-of-care test in general practice.

**Methods:**

The Procalcitonin-Guided Antibiotics in Respiratory Infections (PARI) study is a randomized, single-blinded, non-inferiority, multi-practice intervention study comparing a PCT-group to a control group. Patients (*N* = 508) will be randomly assigned 1:1 to standard care or to the PCT group. The primary outcomes the duration of illness and symptoms from ARTI measured with the Acute Respiratory Tract Infection Questionnaire. Secondary outcomes include (1) Number of participants in each trial arm exposed to antibiotic treatment at index consultation (day 1) and within 30 days, (2) Number of participants in each trial arm with side effects from antibiotic treatment within 14 days, (3) Number of participants in each trial arm with re-consultations within 30 days, (4) Number of participants in each trial arm admitted to hospital (including diagnosis and mortality) within 30 days, (5) Characterization of biomarker (CRP and PCT) level at index consultation. Tertiary outcomes include patient and general practitioner satisfaction with the use of the PCT point-of-care test, and long-term follow-up.

**Discussion:**

To our knowledge, this is the first study to examine a PCT point-of-care test in general practice with the aim of reducing the use of antibiotics in patients with symptoms of ARTI. Results of this study may prove important in targeting antibiotic treatment only to those patients who need it, thus contributing to limiting the spread of antibiotic resistance.

**Trial registration:**

ClinicalTrials.gov Identifier: NCT04216277, date of registration: 2. of January 2020.

## Background

According to the World Health Organization (WHO), antibiotic resistance is a major threat to global health, food security and development [1] which is a serious concern as effective antibiotics are one of modern medicine’s most necessary and lifesaving treatments.

There is close correlation between the use of antibiotics and the development of antibiotic resistance. The primary care sector (not hospital setting) is responsible for most antibiotic prescriptions (approximately 90%) in Denmark, with general practice being responsible for three quarters of these [2]. Therefore, a rational use of antibiotics in general practice is essential in preventing antibiotic resistance. Furthermore, the benefits from rational use of antibiotics also include prevention of possible drug toxicities and conditions such as C. difficile-mediated diarrhea.

One of the main indications for antibiotic use in general practice are acute respiratory tract infections (ARTI) [3, 4]. However, most ARTIs are of viral etiology and antibiotics are often not needed for the patient to recover [5, 6] and may have many negative impacts to both the patient and to society [7, 8]. In selected cases macrolide antibiotics are prescribed by GPs because of their possible anti-inflammatory properties which may be independently beneficial, aside from their antibacterial action [9].

There are at least two major considerations when assessing the appropriateness of antibiotic prescribing in general practice: professional clinical judgement and patient expectations. The general practitioner (GP) must assess several findings such as symptoms, objective findings and paraclinical examinations including C-reactive protein (CRP) levels, leucocyte count or chest x-ray. None of these are specific to bacterial infection [10, 11] and clinical uncertainty regarding management may lead to unjustified prescribing. Pressure from patients may also prompt antibiotic prescriptions [12]. These two considerations may interact.

Most Scandinavian GPs are familiar with the use of CRP measurement and it has been shown that use of CRP guidance can decrease the use of antibiotics for ARTI in general practice [13]. However, CRP is not specific to bacterial infections and CRP levels also rise in cases of other etiologies such as surgery, rheumatic inflammation, viral diseases, systemic illnesses and cancer [14].

Procalcitonin (PCT) is a precursor protein that occurs at very low levels in the blood under physiological conditions [15]. It is, however, correlated with high levels in the blood in cases of serious bacterial infection. It also has a shorter time of release, a shorter half-life than CRP and it is less sensitive to surgery and non-bacterial infection [16, 17]. Studies from general practice have to date shown a reduction in the prescription of antibiotics by PCT-guided antibiotic treatment without significantly prolonging the duration of restrictions in patients’ daily lives due to infection [18, 19]. However, these studies were performed without a PCT point-of-care(POC) test and the test result was not available until hours after the initial patient assessment because it was sent for analysis in a hospital laboratory. Further, these studies were performed in an era when CRP-guided antibiotics were not systematically established.

To our knowledge, the Procalcitonin-guided Antibiotics in Respiratory Infections (PARI) trial is the first to examine a PCT POC test in general practice. The POC element of the intervention may be of crucial importance, since it makes a PCT-guided antibiotic intervention logistically realistic in a primary care setting for the first time.

The aim of this study is to determine whether it is possible to lower the use of antibiotics in patients presenting to their GP with symptoms of ARTI, without significantly prolonging the period of illness by using a PCT POC test.

The PARI study aim is in line with Danish national goals to improve the rational use of antibiotics in general practice [20].

## Methods/Design

### Design, setting and randomization

This study is a randomized, single-blinded, non-inferiority, multi-practice intervention study comparing a PCT group to a control group. We expect the mean duration of ARTI symptoms to be approximately 9 days [21, 22] and we want to detect if this increases to > 10 days in the PCT group i.e. a non-inferiority limit of one day.

The PARI project is a single-blinded study as participants will not be informed of their allocation group: standard care or PCT group. GPs will have access to the PCT results for the intervention group. GPs can tell patients if the biomarker suggests whether antibiotics are needed or not. This is based on the CRP results for both groups and, in the intervention group only, also the PCT levels. Patients will be informed only that “the biomarker” suggests relevant treatment, and other similar generic statements; they will not be informed as to which biomarker the physician refers.

In case of accidental demasking, the investigator will report this as a protocol deviation.

If the PCT level is above 2 ng/L, demasking will deliberately take place because the GP will have to consider referring the patient to hospital on suspicion of serious infection.

At least five practices in two different regions of Denmark, The Capital Region and Region Zealand, will recruit participants, representing both urban and rural areas.

Randomization will be performed by a remote internet-based randomization tool (sealedenvelope.com). The allocation sequence will be stratified by site, age and sex.

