#### Inclusion criteria

The following inclusion criteria must be present:

Age $$\ge$$ 18 yearsAbility to read, understand and willingness to give written consent to participate in the study.Symptoms of acute upper/lower respiratory tract infection (pharyngitis, tonsillitis, otitis media, exacerbations of chronic obstructive pulmonary disease (COPD), or asthma and pneumonia).CRP > 20 mg/mL (based on POC-test in clinic)..

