#### Exclusion criteria

If one or several of the following criteria are present, the participant will be excluded from the study:

The patient is being followed up by a hospital because of verified immune defect or the patient is currently neutropenic (neutrophils < 0,5 mia/L during the last 7 days).The patient has a positive strep A test, (only performed if indicated according to Centor criteria [23].The patient has been treated with antibiotics during the last 14 days up to inclusion.The doctor estimates that the patient needs to be admitted to hospital.The patient is pregnant or breastfeeding..

At any point, the GP will be able to overrule the PCT measurement in the intervention group based on clinical judgement. The reason for deviating from the suggested algorithm must be stated (see Fig. 2).

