### Analysis of procalcitonin

The PCT POC test (ThermoFisher Scientific® PCT Direct, Berlin, Germany) has a functional assay sensitivity (FAS) of 0,22 ng/mL, which is within target range of application in general practice.

The test has two parts: (1) a measuring device (immunochromatography) which analyzes the PCT level in 20 µl of blood (capillary); and (2) a device with a needle to take out 50 µl of blood from the finger and that can be placed directly into the measuring device. Analysis takes 20 min and the only discomfort for the patient is from taking the capillary blood sample from the finger.

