#### Guidance for PCT levels

PCT levels are guided by current literature [16, 17, 26] as follows:

PCT-levels between < 0,25 ng/mL: low risk of bacterial etiology, antibiotic treatment will not be prescribed.PCT levels $$\ge$$ 0,25: bacterial etiology is more likely, antibiotic treatment will be prescribed

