### Time plan

The PARI project recruited the first patient in February 2020. It was estimated that recruitment of all patients would take 18 months. However, the COVID-19 pandemic has paused the study. In Denmark, patients with symptoms of ARTI were triaged by phone or sent directly to COVID-19 clinics in hospitals. Therefore, it is still unclear when we will be able to continue recruiting participants to the PARI project, however, it is expected fall/winter 2021.

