## Discussion

The PARI project is, to our knowledge, the first study to examine a PCT POC test in general practice. Previous studies have examined PCT levels either in a hospital setting or in general practice with a venous blood sample and a prolonged wait for the result. GPs are familiar with POC tests (such as CRP and strep A tests) and these are valuable tools for decision-making in many cases. However, application of PCT as an add-on when an ARTI is not trivial (e.g. CRP values are above 20 mg/L), may aid the GP in ruling out a serious bacterial infection. This could in theory limit GP uncertainties and assist in targeting antibiotics only to the relatively few patients with a high probability of having a bacterial infection and likely to benefit from antibiotic treatment. If this study shows that the PCT-guided antibiotic treatment for ARTI can reduce the use of antibiotics with no safety concerns for the patients (i.e. prove non-inferiority), it will contribute to reaching national goals for improving the rational use of antibiotics in general practice and thereby reduce the development of antibiotic resistance.

Strengths of the study include the randomized controlled trial design that will provide a clear answer regarding the study’s primary objectives. A non-inferiority design has been chosen to examine whether a PCT POC test is not worse than standard care regarding patient safety and duration of symptoms. In addition, we expect PCT testing to reduce the number of antibiotic prescriptions.

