There are some limitations to the study. First, the study is single-blinded, i.e. patients are unaware of the treatment group to which they have been randomized. This is important to minimize reporting bias in the PARI trial as the primary outcome is a patient-reported outcome (recovery). It is impossible in this setup to blind GPs since they need to know which group the patient is randomized to as part of the clinical decision-making process. This information bias could lead to the GP learning from the results of the PCT test and thereby improving their clinical judgement. However, we do not believe such a bias will significantly change the results of the study and the direction of the bias would likely be conservative. Second, the GPs who opt to be included in this study may be more motivated and interested in research and they may be more reluctant to prescribe antibiotics in general, compared to other GPs. This kind of selection bias could affect the results. However, the direction of this bias is also likely to be conservative.

Another limitation to consider is that the analysis of a PCT POC test takes 20 min compared to the CRP measurement, which only takes a couple of minutes. In this study setting we do not consider this a problem, but in the longer term, it could affect the practical use and possible implementation of findings on a wider scale in general practice.

In conclusion, the PARI study is, to our knowledge, the first to examine a PCT POC test in general practice aimed at reducing the use of antibiotics in patients with symptoms of ARTI, without prolonging the symptoms and the duration of restrictions to patients’ daily lives. Since antibiotic resistance is a worldwide health problem, we believe that the results of this study could help to better target antibiotic treatment only to those patients with bacterial infections, which in turn will contribute to limiting antibiotic resistance.

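### Two operative thresholds carry the wrong unit: the PCT demasking and referral trigger (ng/L) and the CRP inclusion criterion (mg/mL)

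*Protocol article*

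**What the plan says.** **PCT trigger.** Design, setting and randomization keeps patients unaware of their group but makes one deliberate exception: "If the PCT level is above 2 ng/L, demasking will deliberately take place because the GP will have to consider referring the patient". The stated reason is suspicion of serious infection. The same section treats accidental demasking as a protocol deviation.

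**Other PCT figures.** Analysis of procalcitonin says that the point-of-care test "has a functional assay sensitivity (FAS) of 0,22 ng/mL". Guidance for PCT levels describes results under its limit as follows: "0,25 ng/mL: low risk of bacterial etiology, antibiotic treatment will not be prescribed". At or above that limit, antibiotics are prescribed.

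**CRP.** Inclusion criteria require "CRP > 20 mg/mL (based on POC-test in clinic". The Discussion describes the setting in which PCT is to be added, an infection that is not trivial, with the example "CRP values are above 20 mg/L".

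**Role of masking.** The Discussion says of patient masking: "This is important to minimize reporting bias in the PARI trial as the primary outcome is a patient-reported outcome (recovery".

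**The concern.** Both numbers belong to rules that someone has to apply. The CRP threshold decides eligibility. The PCT threshold decides when a patient is deliberately unmasked and when the GP must consider hospital referral. It also separates planned demasking from demasking that has to be reported as a deviation.

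Read literally, the PCT trigger would unmask every patient in the PCT arm whose result is at or above the test's functional sensitivity. It would do so in that arm only, because Interventions and timeline adds the PCT measurement only for patients randomized to it. That would weaken the protection the article relies on for a patient-reported primary outcome. The trigger would also fire for patients whom the treatment guidance calls low risk. The CRP criterion, read literally, sets a limit 1000 times the one the Discussion uses.

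**Working it through.** No calculated figure in the article bears on this point. The check is a unit conversion, followed by a comparison of the article's own thresholds. Conversions: 1 ng/mL = 1000 ng/L and 1 mg/mL = 1000 mg/L.

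| Quantity | Section | As printed | Common unit |
|---|---|---|---|
| PCT demasking and referral trigger | Design, setting and randomization | 2 ng/L | 2 ng/L |
| PCT functional sensitivity | Analysis of procalcitonin | 0.22 ng/mL | 220 ng/L |
| PCT limit for withholding antibiotics | Guidance for PCT levels | 0.25 ng/mL | 250 ng/L |
| CRP inclusion threshold | Inclusion criteria | 20 mg/mL | 20,000 mg/L |
| CRP level for adding PCT | Discussion | 20 mg/L | 20 mg/L |

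**Step 1: the trigger against the test.** 2 ng/L = 2/1000 = 0.002 ng/mL. Then 220/2 = 110, so the printed trigger is 110 times below the functional sensitivity. Every result at or above that sensitivity exceeds it.

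**Step 2: the trigger against the treatment rule.** 250/2 = 125, so the trigger is 125 times below the low-risk limit. Results that meet both rules are those above 2 and below 250 ng/L. Within the range the test measures reliably, that leaves 220 to under 250 ng/L, or 0.22 to under 0.25 ng/mL. For example, a result of 0.23 ng/mL (230 ng/L) is low risk with no antibiotic under one rule, and leads to demasking and considered referral under the other.

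**Step 3: the trigger with the unit changed.** 2 ng/mL = 2000 ng/L, and 2000/250 = 8. No result is both above 2000 and below 250 ng/L, so the overlap is empty. The trigger then sits at 8 times the antibiotic cut-off, where a rule for suspected serious infection makes sense.

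**Step 4: CRP.** 20 mg/mL = 20 × 1000 = 20,000 mg/L, and 20,000/20 = 1000. The number is the same in both places; only the unit differs.

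**The case against.** The strongest reply is that these are misprints that no clinician would follow. The article's sensitivity and treatment cut-off for PCT are in ng/mL, so a GP would read the 2 on that scale. The absurdity of the literal reading exposes the slip. The GP need only consider referral, and the article adds that "the GP will be able to overrule the PCT measurement in the intervention group based on clinical judgement". For CRP, the Discussion supplies the right unit. Moreover, "The PARI project recruited the first patient in February 2020", which suggests that the printed criterion was not applied literally. The factors of 110, 125 and 1000 come from a wrong prefix and do not measure any effect on the trial. The Discussion's CRP figure is an example of when PCT may help, not a second eligibility rule. The case report form, the figures and the practice instructions are not shown, so nothing proves that they carry the error.

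Most of this stands, and it limits the importance of the point: the expected harm is small, and there is no evidence that any patient was wrongly demasked or wrongly included. It does not make the printed thresholds right. For CRP, a reader can find the intended unit elsewhere in the article. For PCT, a reader cannot, because the text shown does not state the trigger again. A rule for breaking the blind and considering referral should not depend on the reader's correction. Nor is this detail that an article may leave to a fuller document: the values are stated, and they conflict with other stated values.

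**Conclusion.** The concern holds. Both thresholds are wrong as printed, and the article alone shows it. The PCT trigger of 0.002 ng/mL lies below the test's sensitivity and contradicts the treatment guidance from 0.22 to under 0.25 ng/mL. The CRP criterion is 1000 times the level given in the Discussion.

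That the PCT unit is wrong is firmly established. That 2 ng/mL is the intended value is an inference from the article's other PCT units and from the fact that it removes the conflict. The CRP correction assumes that the Discussion's example refers to the same threshold, which the identical number supports.

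The point should be fixed because it affects eligibility and unblinding rules, but its practical effect is probably small. The 0.25 ng/mL treatment cut-off is not in question. The sample size, non-inferiority margin and analysis are unaffected by these two units.

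**What to change.** - In Design, setting and randomization, change the trigger to above 2 ng/mL, after the investigators have confirmed that value.
- In Inclusion criteria, change the threshold to CRP > 20 mg/L.
- As a precaution, check that the case report form, the two figures and the instructions to practices carry the same units. The Time plan reports that recruitment is paused and expected to resume in fall or winter 2021, so this can be done before further patients enter.

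The cost is a two-item correction note and one check of the operational documents. Design, treatment rule, sample size and analysis need no change.

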#### Interventions and timeline

All participants will receive standard care as per the GPs’ normal procedures and treatments including POCT CRP testing. Patients randomized to the intervention/PCT group will additionally receive diagnostic testing with measurement of PCT.

#### Day 1

Following pre-inclusion assessment, including oral and written information about the PARI study, eligible patients must sign a consent form prior to participation. Subsequently, they will be randomized to either (i) the control group, or (ii) the PCT group. Data-gathering on day 1 will cover participant demographics, the current infection and the likely focus, duration of illness, and assumed etiological micro-organism, objective findings and CRP-level, and results of a self-reported acute respiratory tract infection questionnaire (ARTIQ). In addition, PCT values for the intervention group will be collected on day 1. The control group will receive standard care according to clinical guidelines [24, 25], and the intervention group will receive standard care *plus* PCT-guided treatment (see below).

#### Days 3 and 7

Each participant will be sent a link to the ARTIQ by e-mail on days 3 and 7 (it will also be available in hard copy if required, with responses collated by the investigator). The participants enter their responses into a database (Surveyxact). The content of the ARTIQ is presented in Appendix 1.

#### Days 5 and 15

All participants will be interviewed over the telephone to follow-up on their clinical condition (changes in general condition, fever, pain or coughing), days unable to work, the results of the ARTIQ, and compliance.

#### Day 30

An administrative follow-up to gather information about the use of antibiotics and hospital admissions.

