### Outcomes

#### Primary outcome

Duration of illness and symptoms from an ARTI. The participant-reported primary outcome will be assessed as the number of days until a patient’s daily activities (e.g. work and recreation) are no longer restricted by symptoms from an ARTI. The non-inferiority margin between the intervention group and the control group is set at a one-day difference. The recovery measure will be the specific day indicated by the participants using the validated ARTIQ.

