#### Sample size

A comparable study by Briel et al. [18] showed that the number of days when patients experienced restrictions from an ARTI had a standard deviation of 4 days. The PARI project’s non-inferiority design allows for a clinical non-important difference in sickness of max. 1 day in the PCT group compared to the standard care group. We expect an ARTI to last on average 9 days [21, 22]. The power (1-β) is set at 85% and α at 0.025 (non-inferiority study design). We believe these are relevant estimates since non-inferiority of a PCT-guided antibiotic treatment has previously been demonstrated [18, 19].

The two arms of the study will be randomized 1:1 with 231 participants in each arm. We estimate that 10% of participants will not complete the project, so a total of 508 participants will be needed.

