#### Statistical analysis

An intention-to-treat (ITT) and a per-protocol (PP) analysis are planned. Chi-square tests for binary effects and t-test or Mann-Whitney U-test for interval scale effects will be used (depending on distribution).

We will also present descriptive statistics in the different subgroups such as sex, age, and demographic variables.

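### Allocation is stratified by site, age and sex, but the named tests ignore these factors, which makes the comparison conservative to the extent that they predict outcome

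*Protocol article*

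**What the plan says.** Under Design, setting and randomization, the protocol article states: "The allocation sequence will be stratified by site, age and sex". The same section plans for "At least five practices in two different regions of Denmark".

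Under Statistical analysis, the comparisons are named: "Chi-square tests for binary effects and t-test or Mann-Whitney U-test for interval scale effects will be used (depending on distribution". Sex and age return in that section only for description: "We will also present descriptive statistics in the different subgroups such as sex, age, and demographic variables". The article names no regression model, stratified test or covariate.

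Under Interventions and timeline, baseline information is planned before any outcome is known: "Data-gathering on day 1 will cover participant demographics, the current infection and the likely focus, duration of illness". The same day-1 list includes CRP and the ARTIQ.

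The primary comparison is judged against a fixed limit: "The non-inferiority margin between the intervention group and the control group is set at a one-day difference". The Sample size section takes an SD of 4 days from an earlier general-practice trial and sets 85% power and α of 0.025, with 231 participants per arm and 508 in total after allowing for 10% not completing.

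**The concern.** Stratified allocation balances the arms within strata. This removes the between-stratum part of the variance from the true sampling error of the treatment difference. A two-sample t-test still counts that part in its standard error. The reported interval is then wider than the design justifies, and the test runs below its nominal level. A plain chi-square test does the same for the binary outcomes. Site may matter most for antibiotic exposure, because the GP decides on prescribing and may overrule the PCT result.

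In a non-inferiority trial the upper confidence limit decides the result. Needless width can make a truly non-inferior strategy miss the 1-day margin. What is at stake is power, not a false claim of non-inferiority.

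**Working it through.** **Inputs from the protocol article.** Margin 1 day (Primary outcome); SD 4 days, α 0.025, power 85%, 231 per arm, 508 in total, 10% loss (Sample size).

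**Assumptions.** True difference 0; α taken as one-sided; balance within strata. R² is the share of the variance in days to recovery explained by site, age and sex. The document gives no value, so a range of 0 to 20% is shown.

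**1. The plan's own figure.** n per arm = 2 × 4² × (z₁₋α + z₀.₈₅)² / 1².
- One-sided 0.025: 32 × (1.960 + 1.036)² = 287.3, so 288.
- One-sided 0.05: 32 × (1.645 + 1.036)² = 230.1, so 231.

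The stated 231 is therefore not reproduced at the stated α; it fits one-sided 0.05. At one-sided 0.025, 231 per arm gives 76.6% power. The total of 508 is 462 × 1.10 = 508.2. Taking 10% off 508 leaves 457.2, or about 229 per arm, which is used below.

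**2. Standard errors at 229 per arm.**
- Reported by the unadjusted test: SE_u = 4 × √(2/229) = 0.374.
- True under stratified allocation, and reported by an adjusted model: SE_a = SE_u × √(1−R²).
- Ratio SE_u/SE_a = 1/√(1−R²).

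**3. Power and level.**
- Unadjusted power = Φ[(1 − 1.96 × SE_u)/SE_a].
- Adjusted power = Φ[1/SE_a − 1.96].
- True one-sided level of the unadjusted test = Φ[−1.96/√(1−R²)].

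Example at R² = 10%: SE_a = 0.374 × √0.9 = 0.355. Unadjusted power is Φ[(1 − 0.733)/0.355] = Φ(0.754) = 77.5%. Adjusted power is Φ(0.860) = 80.5%.

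| R² from strata | Interval too wide by factor | Unadjusted power | Adjusted power | Gain (points) | True level, unadjusted |
|---|---|---|---|---|---|
| 0 | 1.000 | 76.3% | 76.3% | 0 | 2.5% |
| 5% | 1.026 | 76.8% | 78.4% | about 1.5 | 2.2% |
| 10% | 1.054 | 77.5% | 80.5% | about 3 | 1.9% |
| 20% | 1.118 | 78.8% | 84.9% | about 6 | 1.4% |

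The unadjusted power also rises with R², because stratification itself reduces the true sampling error. The gain from adjustment must therefore be read along each row, not from the 76.3% in the top row.

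**4. Simulation check.** With 462 patients, 20 balanced strata, R² = 10% and 4,000 runs per setting, power was 77.5% unadjusted and 80.4% adjusted, and the one-sided type I error was 0.020 and 0.024. The formulas at 231 per arm give 77.8% and 80.8%.

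**5. Baselines not stratified on.** For illness duration before inclusion, baseline ARTIQ and CRP, allocation does not force balance. Chance imbalance in them is real sampling variation, and the unadjusted standard error rightly includes it. Coverage and level stay nominal. Adjusting for them shortens the interval, but leaving them out is not an error, and the last column of the table does not apply to them.

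**The case against.** The strongest objection is that a journal article condenses the full protocol. It nowhere calls the analysis unadjusted, and a fuller document could add covariates. This stands in part: nobody can say from the article that the final analysis will be unadjusted. But the article is not silent. It names the tests that are to be used, and those tests do not match the allocation scheme that it describes.

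It is also true that the size is undocumented. At R² = 0 nothing is lost, and nothing in the article shows that site, age and sex explain as much as 20% of illness duration. This stands, and is why a range is given.

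A reader might infer three stronger things, which the document does not support:
- *The trial could wrongly declare non-inferiority.* It could not for this reason: the level of the unadjusted test stays at or below 2.5%.
- *Adjustment lifts power from 76% to 85%.* This compares two different values of R². At R² = 20% the unadjusted test already has 78.8%.
- *Omitting illness duration, ARTIQ or CRP makes the interval too wide in the same sense.* It does not; it only forgoes precision.

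**Conclusion.** The point holds as a mismatch between design and stated analysis. Its effect is a loss of efficiency that depends on how far site, age and sex predict outcome. Under the assumptions above, the loss is nil at R² = 0, about 1.5 points of power at 5%, 3 at 10% and 6 at 20%. The interval is 2.6%, 5.4% and 11.8% too wide at the last three values. The error is conservative.

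Power of about 76% against the stated 85% has a different cause, namely that 231 per arm does not fit the stated α. At 231 per arm, adjustment alone would bring power back to 85% only if R² reached about 0.196, so it cannot stand in for correcting that section. The change is worth making because it costs little and the trial has no precision to spare.

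**What to change.** Amend the Statistical analysis section:
- **Primary outcome.** Name a linear model for days to recovery with treatment, site, age and sex, plus prespecified day-1 baselines such as illness duration before inclusion and ARTIQ score (CRP may be added). Report the adjusted mean difference with its 95% CI and compare the upper limit with 1 day.
- **Binary outcomes.** Replace the plain chi-square test as the main comparison with a risk difference adjusted for, or stratified by, the same factors. A standardised estimate from a logistic model or a Mantel-Haenszel estimate would serve.
- **Prespecification.** Fix the covariate list and the coding of age before the data are analysed.

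The cost is wording only. Site, age and sex are needed for randomisation, and the other variables are already collected on day 1. Separately, reconcile the stated power, α and sample size in the Sample size section.
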